# Age-sensitive telehealth group therapy for depression in older adults with and without comorbid anxiety (VISION-AGE): study protocol for a randomized controlled trial in an embedded mixed-methods design

**DOI:** 10.1186/s12888-026-07851-2

**Published:** 2026-02-18

**Keywords:** Online psychotherapy, Comorbid depression and anxiety, Digital mental health intervention, Life review therapy, Life planning

## Abstract

**Background:**

There is a necessity to enhance psychotherapeutic treatment approaches for older adults with depression, particularly those exhibiting comorbid anxiety, in both clinical practice and healthcare provision. The aim of the clinical study VISION-AGE is to investigate the efficacy and mechanisms of action of an age-sensitive online group psychotherapy for adults aged 68 + with clinically significant depression (with or without anxiety).

**Methods:**

In a two-arm randomised controlled trial, the hypothesis that enriched life-review therapy, offered in a video-conference group setting, is superior to an active control group, will be tested. Following randomisation into the intervention or control group, all participants attend weekly manual-guided online group sessions for 20 weeks (plus four additional individual meetings) in fixed groups of four participants. In the intervention group, participants are administered psychotherapy, with a focus on promoting self- and developmental regulation strategies (i.e., positive self-perceptions of ageing next to reminiscence, life management and life planning). The active control group takes part in a standardised non-clinical discussion programme promoting peer support and socializing, similar to typical social care services for older adults. The planned sample size is *N* = 250 (*n* = 125 participants per arm). The hypothesized reduction of self-reported depressive symptoms (primary outcome), anxiety as well as clinician-rated depressive symptoms and the hypothesized improvement of psychological well-being (secondary outcomes) will be assessed at baseline, post-treatment and at the 6-month follow-up. Furthermore, qualitative interviews will be conducted with participants of the intervention group in order to gain a more profound understanding of the subjective change processes experienced during the intervention.

**Discussion:**

VISION-AGE explores the potential of online group psychotherapy to address the needs of older adults with clinical depression. Whilst online therapy facilitates convenient access for patients, group therapy format enables therapists to extend their reach. The study will provide practical implications to improve access to and quality of psychotherapeutic care for this under-resourced population. The long-term objective is the development of a transdiagnostic psychotherapeutic programme that is both efficient and cost-effective, and which is accessible and appealing to older patients in regular mental health care.

**Trial registration:**

at The German Register of Clinical Studies (DRKS); 13 November 2025 (Identifier: DRKS00038366; https://www.drks.de/DRKS00038366). Scientific title: Efficacy and modes of action of an age-sensitive telehealth group therapy to reduce clinical depression (with and without anxiety) in older adults (VISION-AGE).

**Supplementary Information:**

The online version contains supplementary material available at 10.1186/s12888-026-07851-2.

## Background

Due to demographic shifts, older adults now make up a growing proportion of the patient population, particularly in light of their substantial medical needs. Approximately one in three older adults has experienced a mental health disorder within the past year, with depression and anxiety being particularly prevalent [1]. A recent review and meta-analysis found a pooled prevalence of 31.7% (95% Confidence Interval [27.90, 35.59]) for depression alone (including mild depression) in the older population worldwide [2] — commonly termed geriatric or late-life depression. Depression in older adults has been shown to be associated with an increased risk of physical morbidity, suicidal ideation, physical and cognitive decline, social isolation, inadequate self-care, and functional impairment [3], resulting in significant welfare costs [4]. Similarly, anxiety disorders are common in late adulthood (affecting around 17% of the population) and are also associated with various cognitive disadvantages, as well as physical and social limitations [5, 6]. Furthermore, there is extensive evidence of frequent comorbidity of depression and anxiety among older people, up to 50% [7], whereby the symptoms often reinforce each other, maintaining negative effects [8].

Substantial deficits remain in the development and implementation of adequate, effective and efficient psychotherapeutic approaches that specifically target older adults, a group that is both under-researched and under-supplied [9–11]. Mental disorders in older adults remain frequently underdiagnosed and inadequately treated across all care settings, often without adherence to established guidelines. Pharmacological treatments predominate, with inadequate medication, side effects, and polypharmacy commonly occurring [12]. The factors contributing to the undersupply are numerous, but include a paucity of appealing treatment offers that target the needs and preferences of patients in later life, a lack of treatment settings that allow mobility-impaired patients to receive treatment in their own home (e.g. home treatment, digital therapy), insufficient referral to psychotherapy by general practitioners and a lack of clinical training programmes for psychotherapists [13].

Our age-sensitive VISION-AGE programme, an enriched life review therapy (LRT) for the primary treatment of depression (with and without anxiety) offered in a videoconference group setting, aims to address and reduce the following research gaps: According to systematic reviews and meta-analyses, standardized interventions for (face-to-face) treatment of depression in older people based on a standardized treatment manual are superior to passive control groups and conventional treatment in terms of their efficacy [14, 15]. Cognitive behavioral therapy (CBT) [16], life review therapy (LRT) [17], and problem-solving therapy [18] have proven most (and similarly) effective. However, when compared to active control groups, pre-post effect sizes are usually significantly smaller (around d = 1.0) [15, 19]. In a very recent randomised controlled trial (RCT) in Germany, a late-life specific CBT intervention (‘CBTlate’) was not superior to non-specific supportive psychotherapy (empathic listening; *N* = 251) [20]. Conversely, this implies that further evidence is needed to validate the specific efficacy of psychotherapeutic treatments for this population and to assess their advantages over cheaper interventions like community-based support groups for older adults. A control group should build on the current state of research in this area and currently, there is no scientifically based standard treatment for late-life depression – especially not in a group setting. When it comes to non-pharmacological services, social group offers correspond most closely to what older adults typically receive under naturalistic conditions in elderly care. Therefore, research needs to test the benefits of group psychotherapy over cheaper interaction offers, like social groups, for this population.Until now, treatment programmes have focused almost exclusively on depression in older patients, since comorbidity is commonly associated with poorer treatment outcomes. Given the high comorbidity of anxiety and depressive disorders [7], a transdiagnostic approach improves the generalisability of the findings and their applicability in outpatient settings.Only four preliminary RCTs have assessed the efficacy of psychological interventions for comorbid depression and anxiety disorder [21]. Further research is therefore needed to determine whether a transdiagnostic programme can effectively address symptoms of both depression and anxiety simultaneously.A recent study showed that older patients with depression were more likely than younger individuals to set personal treatment goals aimed at improving their wellbeing and coping with their personal development [22]. Further research is needed to investigate whether psychotherapy that is tailored to age-specific treatment goals, such as improving well-being and encouraging reminiscence, is more effective than regular psychotherapy.So far, life review therapy is the only therapeutic approach to have used findings from lifespan psychology [23], but it has not yet taken all current empirical research findings into account. Reminiscence in older adults, as promoted in life review therapy, has been shown to be prospectively associated with higher levels of life satisfaction and lower levels of depression and anxiety [24]. Other adaptive strategies of self- and developmental regulation (well-researched in lifespan psychology) have not yet been adequately integrated in treatment programmes:There is ample evidence of a significant association between internalised age-related stereotypes and health outcomes [25]. Therefore, it is important to foster a positive self-perception of ageing to avert adverse health-developments and promote well-being.SOC-strategies for life-management (i.e., *s**electing* positive and subjectively meaningful aspects of life, *optimising* existing abilities, and *compensating* for deficits) have been shown to be associated with feelings of satisfaction and positive affect in old age [26].Moreover, research shows that future planning tends to decline with age in favour of a stronger focus on the present – although planning is associated with higher levels of well-being and lower levels of depression and anxiety [27].Consequently, research should examine whether the augmentation of live-review therapy with these three adaptive strategies (i.e. the enhancement of positive self-perceptions of ageing, the strengthening of SOC-strategies and life-planning) yields therapeutic benefits for older patients.The most recent systematic review on group psychotherapy with older adults [28] included nine controlled studies on the effectiveness of group psychotherapy for late-life depression (defined as 60+). Four of these studies employed a randomised controlled trial design. The systematic review excluded studies involving mental health comorbidities (with the exception of anxiety disorders) and comorbid cognitive impairments. The predominant therapeutic approaches employed were CBT and LRT (also referred to as reminiscence therapy). The extant research demonstrated a significant reduction in depressive symptoms in group therapy, with only one exception. The findings were consistent across diverse settings, encompassing outpatient, inpatient, and nursing facility demographics, as well as individuals across the age spectrum from “young old” to “old old”. Nevertheless, superiority over other psychosocial approaches or active control groups, such as relaxation groups or discussion groups, was not demonstrated in all studies. In addition to the observed reduction in depressive symptoms, a number of the included studies identified favourable outcomes with regard to anxiety, integrity, and life satisfaction. The stability of the achieved improvements remains unconfirmed, as only a limited number of studies have reported follow-up (FU) surveys with equivocal results and in some cases high rates of attrition. Despite the limited evidence, it remains important to investigate the therapeutic benefits of group therapy, as, in contrast to individual therapy, it has a particular potential for this age group. Life-span developmental research has demonstrated that older adults tend to distance themselves in their self-definition from their own age-group [29]. Consequently, the formation of groups has advantageous potential to enhance interpersonal relationships, foster trust, and promote both age identity, which is based on shared experiences and life stages [30], and generational identity, based on being born at the same time [31]. Furthermore, the utilisation of model learning and the collective ego of the group facilitates a more nuanced evaluation of situations, thereby enabling participants to develop more efficacious strategies for addressing typical age-related challenges. In light of this, further research is required to investigate the long-term effectiveness of group psychotherapy involving older adults of the same life stage and cohort.It is evident that there is a significant absence of research in the domain of digital e-mental health interventions for the elderly. A 2023 systematic review [32] identified a total of five RCTs that examined the efficacy of virtual (e.g. telephone, videoconference, or internet-based) non-pharmacological interventions in reducing symptoms of depression in older adults (defined as ≥ 60) – the authors summarise paucity in this research field. In the specific case of videoconference psychotherapy, the efficacy and non-inferiority in comparison to face-to-face therapy for depression and anxiety disorders has been empirically substantiated for younger patients through meta-analyses. For example, in a meta-analysis of video-based CBT treating comorbid depression and anxiety, large effects were found for depressive symptoms (g = 0.79) and anxiety (g = 0.82) [33]. A systematic review of the literature shows that group therapy, in small formats, can be effectively delivered online [34]. The necessity for well-controlled efficacy studies on video-based psychotherapy for older patients is evident, as this type of support could give a larger group of older adults access to psychotherapy, including people with reduced mobility, those living in rural areas and older carers unable to leave home for face-to-face therapy and accompanying travel requirements.

In light of the aforementioned research gaps, the implementation of a video-based group psychotherapeutic programme targeting older adults with depression and comorbid anxiety constitutes a pioneering intervention – particularly in light of the high clinical care demand. In terms of the VISION-AGE programmes’ content, the rationale focuses on improving adaptive forms of self- and developmental regulation strategies. These are outlined as follows: (1) positive self-perceptions of ageing, (2) life review (strengthening reminiscence), (3) life management (training SOC-strategies) and (4) life planning. This approach is embedded within a therapeutic concept that traverses the three biographic ‘time corridors’ past - present - future. The primary therapeutic methods originate from LRT, but were enriched by CBT and therapeutic techniques of Positive Psychology (PP).

In order to develop an efficient psychotherapeutic programme, it is crucial to examine how patients interpret, memorise and realise the psychological input received over the course of a treatment. In this regard, qualitative methodologies provide insight into the individual patient’s perspective on the therapeutic change [35]. Therefore, the present study employs a mixed-methods approach, triangulating quantitative and qualitative methodologies.

In the context of this innovative therapeutic concept, and considering that the manual for the control group represents an adapted extension of an already proven helpful concept [36], the potential benefits and study objectives are the reduction of symptoms of depression, anxiety as well as the increase of psychological well-being and concepts of self- and developmental regulation. No health risks are expected to be associated with data collection or the programme, as all participants will receive support. As participants in both conditions will be dealing with personal issues and each other, temporary mood deterioration may occur. However, given the qualifications, training and supervision of our group therapists (leading the intervention group) and group facilitators (leading the control group), no significant long-term harms or deterioration are expected, even after the programme ends.

### Objectives

The main objective of the present study is to investigate the effectiveness of the age-sensitive telehealth group psychotherapy (VISION-AGE) for older adults with depression (with or without comorbid anxiety) compared to a non-clinical active control condition (a group discussion programme) with regard to depression, anxiety, and psychological wellbeing. Furthermore, the mechanism of action of VISION-AGE will be investigated. Adaptive self- and developmental regulation strategies (defined as positive self-perceptions of ageing, reminiscence, life management, and future planning) are examined as mediators, based on the assumption that strengthening these capacities play a central role in reducing symptoms of depression and anxiety, while enhancing psychological well-being. The influence of comorbidity and the severity of depressive symptoms on the programme’s effectiveness will be explored through exploratory analyses. A mixed-methods approach is applied to relate older patients’ subjective experiences of change processes during the psychotherapy (as assessed by semi-structured interviews) to their psychometric treatment outcomes.

This large-scale superiority RCT is expected to provide robust evidence in support of the hypothesis that the intervention improves patient outcomes, thereby offering valuable guidance for the development of future healthcare policies. Consequently, the intervention is accompanied by a health economic evaluation. The hypotheses and questions to be examined in the study are presented in Tables 1 and 2.

**Table 1 Tab1:** Overview of hypotheses in sub-study 1 (quantitative component of the mixed-methods design)

Hypothesis	Description
Main Hypothesis 1 H1a H1b	Our videoconference-based group-psychotherapy programme VISION-AGE (i.e., enriched LRT intervention group, IG) leads to greater reduction in • self-reported depression symptoms (primary outcome) and • clinician-rated depression symptoms (secondary outcome) compared to a videoconference-based non-clinical group discussion programme (i.e., active control group, CG) at post-treatment and 6-month FU, with moderate between and moderate-to-large within effect sizes for VISION-AGE, while we assume that both conditions lead to significant reduction in depression over time.
Hypothesis 2 H2a H2b	The VISION-AGE programme leads to • a greater reduction in anxiety symptoms and • a greater improvement in psychological well-being compared to the active control group at post-treatment and 6-month FU.
Hypothesis 3 H3a H3b H3c H3d H3e	The effectiveness of VISION-AGE is mediated by an improvement of self- and developmental regulation, as assessed in a standardized manner (i.e., • positive self-perceptions of ageing, • reminiscence, • life management, • future planning as mechanisms of action). The effect is most pronounced respectively in those participants who had lower baseline scores in these variables.

**Table 2 Tab2:** Research questions in the mixed-methods design (quantitative and qualitative)

Research question	Description
Research question 1	Which subjectively experienced processes of change arise in the participants everyday life by participating in VISION-AGE?
Research question 2	How are the subjectively experienced processes of change related to the primary outcome?
Research question 3	Merging the results from study 1 and 2 (triangulation): How effective is VISION-AGE, and what are objective (measured via standardized instruments) and subjective (in the participants’ personal experience) mechanisms of action?
Research question 4	Explorative cost-effectiveness analysis: How cost-effective is VISION-AGE compared to the CG?

## Methods

This study protocol is reported in accordance with the SPIRIT (Standard Protocol Items: Recommendations for Interventional Trials [37] and the CONSORT (Consolidated Standards of Reporting Trials) statement [38] for transparent reporting of parallel-group randomised trials.

### Study design and timeline

The study is planned as a two-armed RCT with two groups, testing in Germany the superiority of the IG above a non-clinical, active CG. The IG includes therapist-guided psychotherapy, the CG comprises an active online discussion programme carried out by senior citizen assistants. A mixed-methods design, integrating both quantitative and qualitative data collection methodologies, will be employed. The study is planned to last 36 months, from 1 December 2025 to 30 November 2028, with recruitment continuing steadily until the target sample size is reached, overlapping with the intervention phase. As a fully online intervention, the trial enables nationwide recruitment across Germany. Participants can take part in the study from home using a suitable device. Figure 1 shows the trial procedure as a flow chart.

The study centre will be located at the Departments of Psychology at MSB Medical School Berlin and the University of Siegen. The group therapists and group facilitators can decide where to carry out digital interventions, as long as they are in a quiet space that ensures data security and privacy.

**Fig. 1 Fig1:**
[figure not shown]
Flowchart of the VISION-AGE study design and participant allocation

### Power and sample size

The study will aim to include 250 participants, with 125 allocated each to the IG and the CG, thereby ensuring a minimum of 100 completed data sets for each intervention at the FU. The plan is founded upon a priori sample size calculation, which yielded a total of 200 participants following a 1:1 randomisation ratio. However, the drop-out-rate must also be considered, which is estimated at 20%, based on the findings of previous studies, for example, 17% in a study with older adults experiencing depression and anxiety [36].

The sample size calculation is based on the assumption of a medium-to-large pre-post (“within”) effect size (d = 0.75) for VISION-AGE and a moderate “between” effect size (d = 0.45) for the contrast (pre-post change in the IG compared to pre-post change in the CG). It is hypothesised that the proposed programme, considered an enhanced form of LRT, will demonstrate effect sizes that are at least commensurate with those observed in LRT, and approximately equivalent to those reported for CBT: The large pre-post effect size, as found for CBT (d = 1.06) and LRT (d = 1.0) in late-life depression [16] will somewhat be reduced due to the possible comorbidity with anxiety and the video-based format (e.g., g = 0.79 for depression and g = 0.82 for anxiety, meta-analysis) [33]. The group setting additionally reduces the effect size in late-life depression (e.g., d = 0.65) [39]. However, since we are planning very small groups and additional individual sessions, we estimate a within effect size of no less than d = 0.75 and a between effect size of d = 0.45.

For statistical tests on the α = 5% level, with a total sample size of *N* = 200 (100 per arm), power simulations using R package Superpower [40] yielded a power > 0.90 for both main effect and the interaction regarding a 2 (condition) by 2 (time) mixed Analysis of variance (ANOVA), as well as power > 0.80 for the main contrast of interest (i.e., the pre-post change in the IG in comparison to the pre-post change in the CG).

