### Randomization and blinding

Participant eligibility is determined during the enrolment interview by a member of the research team, based on the inclusion and exclusion criteria. This information will be communicated to the participant and recorded in the data capture system. Following this evaluation, suitable participants are then randomly assigned to a study condition using a computer-generated simple randomisation algorithm. The research team has no influence on the allocation of suitable participants to one of the conditions. Within the specified conditions, patients are manually allocated to a block of four participants each, taking into account their time availability for group therapy. After the enrolment interview digital visits via videoconference will be carried out at baseline (T1) and post-treatment (T6) and FU (T7) by members of the research team who will be blinded to the group allocation and previous test results. The study data capture system implements a role-based access concept to ensure that details of group allocation and participants’ recorded data are only accessible to the Principal Investigator (PI) and research team members responsible for supervision.

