### Statistical analysis sub-study 1 (quantitative study)

Statistical analyses regarding sub-study 1 will be based on intention-to-treat (ITT) as well as on per-protocol analyses. The primary analysis will be ITT. To compensate for panel attrition and item-nonresponse, missing data will be multiply imputed in all ITT analyses. Imputation models will be fully compatible to the subsequent analysis models (i.e., substantive model compatible multiple imputation) and will include all relevant associations (like interaction terms) and will represent the clustered structure of the data. The main substantive model of interest is a (generalized) linear mixed effects model, which evaluates stability and change in the outcome variables over time depending on experimental condition. The focal effect of interest in this model is the time by condition interaction. To interpret this effect, we especially look at the following contrast: the pre to post change in the experimental condition in comparison to the pre to post change in the control condition (i.e., a contrast over two contrasts). Additionally, pre-post and pre-FU effect sizes (Cohen’s d) will be calculated for all outcome-variables for both groups (IG and CG) to further quantify the found effects. In additional (exploratory) analyses, we will test for possible effects of gender, age, education, comorbidity and severity of comorbid symptoms. We also explore possible interactions of the outcome variables by means of parallel longitudinal path modelling. If the first two hypotheses can be confirmed, hypothesis 3 (regarding the underlying therapeutic mechanisms) will be evaluated by mediation and moderation analyses using path models.

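### The stated power treats the 200 participants as independent, although both arms are treated in fixed groups of four with a shared leader, so it is not established for this design

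*Protocol article*

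**What the plan says.** Under Power and sample size, the protocol article assumes a "medium-to-large pre-post (“within”) effect size (d = 0.75) for VISION-AGE". For the comparison of the arms, its assumption is "a moderate “between” effect size (d = 0.45) for the contrast (pre-post change in the IG compared to pre-post change in the CG". The test level is given as "For statistical tests on the α = 5% level". The calculation is one "which yielded a total of 200 participants following a 1:1 randomisation ratio", and power was simulated "regarding a 2 (condition) by 2 (time) mixed Analysis of variance (ANOVA), as well as power > 0.80 for the main contrast of interest"; the interaction and main effects are put above 0.90. The target is then raised to 250 for an expected 20% drop-out, "thereby ensuring a minimum of 100 completed data sets for each intervention at the FU". The group setting enters this section only as a reason to lower the assumed effect size.

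Under Randomization and blinding, after individual randomisation "patients are manually allocated to a block of four participants each", according to when they are available. The Intervention section has both arms meet weekly for 20 sessions in these fixed groups. The individual meetings are held with the same group therapist or group facilitator.

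Under Statistical analysis sub-study 1, the imputation models are to be compatible with the analysis models and "will represent the clustered structure of the data". The analysis model is a (generalized) linear mixed model for time by condition. The article does not say which clusters are meant.

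**The concern.** A two-by-two mixed ANOVA accounts for the two measurements on one person. It assumes that different people are independent. Here four people share 20 sessions and a leader, and the Discussion expects the group itself to act on mood and notes that single members may strongly influence group dynamics. Those are the conditions under which outcomes within a group become correlated. Leaders may also run several groups; the article does not say how many.

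If the final analysis models that correlation, the test pays a price that the power figure leaves out. This matters because the comparator is active and the Background cites a recent late-life trial that found no superiority over supportive therapy. A null result here would be read against the power the article states.

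**Working it through.** **Inputs from the article:** difference in pre-post change d = 0.45; 100 completers per arm; α = 5% (two-sided assumed); 125 randomised per arm; drop-out 20%; groups of four in both arms.

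**Assumptions, because the article gives no value:** pre-post correlation r, ICC of the change score within group, ICC within leader, and number of leaders L per arm.

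**Reproducing the plan.** Drop-out: 200 / (1 − 0.20) = 250, exact, so nothing is left over for clustering. For independent participants, the SD of change in units of the outcome SD is √(2(1 − r)), and the standardised change difference is δ = 0.45 / √(2(1 − r)). At r = 0.5, δ = 0.45. The noncentrality is 0.45 × √(100/2) = 3.18 on 198 degrees of freedom, and power is 0.886. The claim of more than 0.80 is reproduced. The claim of more than 0.90 needs r above about 0.52–0.53, even without clustering.

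**Retained group size.** 125 per arm is about 31 groups. A 20% loss leaves 4 × 0.8 = 3.2 per group on average. If losses are random, sizes vary with variance 4 × 0.8 × 0.2 = 0.64, and the size-weighted mean is (0.64 + 3.2²) / 3.2 = 3.4. So m is taken as 3.2 to 3.4, not 4.

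**Group clustering.** Design effect DE = 1 + (m − 1) × ICC; effective n per arm = 100 / DE. Example at m = 3.2, ICC 0.10: DE = 1 + 2.2 × 0.10 = 1.22; effective n = 82.0; noncentrality 0.45 × √(82.0/2) = 2.88; power 0.82.

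| r (assumed) | no clustering | ICC 0.05 | ICC 0.10 | ICC 0.15 |
|---|---|---|---|---|
| 0.4 | 0.82 | 0.78 | 0.74 | 0.70–0.71 |
| 0.5 | 0.89 | 0.85 | 0.81–0.82 | 0.77–0.78 |
| 0.6 | 0.94 | 0.92 | 0.89 | 0.86–0.87 |

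**Where 0.80 is lost.** At r = 0.5, power of 0.80 needs 78.5 independent participants per arm. The tolerable DE is 100 / 78.5 = 1.274, so the tolerable ICC is 0.274 / 2.2 = 0.125 (m = 3.2) or 0.274 / 2.4 = 0.114 (m = 3.4). The same steps give an ICC of about 0.03 at r = 0.4 and about 0.25 at r = 0.6.

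**Adding leaders.** DE = 1 + (m − 1) × ICC_group + (100/L − 1) × ICC_leader, here with ICC_group 0.05, ICC_leader 0.02 and r = 0.5. The last column uses 2L − 2 degrees of freedom.

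| leaders per arm (assumed) | DE | power | power, leader-level df |
|---|---|---|---|
| 6 | 1.42–1.43 | 0.75 | 0.67 |
| 8 | 1.34–1.35 | 0.78 | 0.72 |
| 12 | 1.26–1.27 | 0.80 | 0.77 |
| 16 | about 1.22 | 0.82 | 0.79–0.80 |

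**If clustering were left out of the analysis.** The type I error is about 2 × (1 − Φ(1.96 / √DE)): 6.3% at DE 1.11 (ICC 0.05, m = 3.2) and 7.8% at DE 1.24 (ICC 0.10, m = 3.4).

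**The case against.** The strongest reply is that the claim for the main contrast is a lower bound, and at r = 0.5 there is reserve: 0.89 falls below 0.80 only when the group ICC exceeds about 0.11 to 0.12. This stands. A reader might infer that the trial does not reach 0.80; the article gives no ICC, no r and no number of leaders, so that cannot be concluded.

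A reader might also infer that the claim above 0.90 fails at every ICC. That is true only for r up to about 0.52. At r = 0.6, power is still 0.92 at ICC 0.05.

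The planned analysis may also recover information. It is by intention to treat, with multiple imputation for all 250 and PHQ-9 scores at seven time points. As an upper bound, 125 per arm in full groups of four at ICC 0.10 (DE 1.30, effective n 96.2, r = 0.5) gives 0.87. The truth lies between that and the completer figure of 0.81–0.82. This softens the loss but does not remove it, because the article's own figure is for 200 completers.

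Finally, the analysis section mentions clustering. The wording concerns the imputation models, but their stated compatibility with the analysis models points towards clustering being modelled. So the documents do not support the inference that the final test will ignore it. Nor would it be a finding that a condensed article omits random-effect details. What remains is that the article states a power figure together with the model behind it, and that model does not match the design.

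**Conclusion.** The omission holds. For any positive within-group or within-leader correlation the stated power is too high, and it is not established for this design. It is an omitted design feature, not an arithmetic slip: 200 / 0.80 is 250, and the unclustered power exceeds 0.80 at r = 0.5.

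The loss is moderate. At r = 0.5 with about 3.2 to 3.4 retained per group, it is 3 to 4 percentage points at ICC 0.05 and 7 to 8 at ICC 0.10. It grows if few leaders carry many groups. Power above 0.80 is credible for small to moderate group ICCs with little leader effect. Power above 0.90 depends first on a pre-post correlation that the article does not state. All of this rests on assumed ICCs, r and leader numbers. Severity is moderate.

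**What to change.** Keep N = 250.

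- Rerun the simulation with therapy group and leader as levels in both arms. State the pre-post correlation, the planned number of therapists and facilitators, and a range of group and leader ICCs.
- Replace the two single power figures with the resulting range.
- Add one sentence under Statistical analysis sub-study 1 saying that the clustered structure includes therapy group and leader, and that both are carried into the primary mixed model as well as the imputation models. Leaving them out would push the type I error above 5%.

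The cost is one rerun, a reworded power paragraph and one added sentence. The stated power becomes less favourable. No extra participants are needed and trial conduct does not change.
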